### Sample size determination

The sample size has been calculated on the basis of Fleming’s single-stage procedure [16] and considers the sample size required to assess the change in the experimental group. The control group provides evidence of the learning effect due to repeated assessments. The proposed study seeks to determine effect sizes in relation to the primary outcome measures to enable informed designing of subsequent larger studies. This study is therefore not powered for formal statistical comparison of placebo and study drug groups.

We estimate the learning effect (i.e., the proportion of patients whose memory function improves due to familiarity with the assessments) to be slightly less than 0.15. A proportion of less than 0.15 in the intervention group would therefore indicate that the intervention (everolimus in the treatment of neurocognitive problems in tuberous sclerosis) does not warrant further investigation. A proportion of at least 0.35 would provide sufficient evidence for further investigation of this intervention. Values between these would be discussed in depth by members of the trial team.

Therefore, to test the null hypothesis that the proportion of patients in the intervention group who improve their memory function by 1 SD is at most 0.15 against the alternative hypothesis that the proportion of patients in the intervention group who improve their memory function by 1 SD is at least 0.35, with 80 % power and a one-sided α of 0.05, we require a total sample size of 48 (i.e., 32 who receive the intervention and 16 control subjects). This sample size is inflated to allow for 20 % loss to follow-up.

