### Statistical methods

#### Main analysis

All randomised participants who received at least one dose of study drug will be included in the data analysis. Patients will be analysed according to the treatment they received. We will present data descriptively and determine effect sizes. Results will be presented split by trial arm.

The primary outcome of this study is memory function with improved memory function classed as a 1-SD response on any of the memory tests listed in Table 3. A one-sample chi-square test will be used to determine whether the proportion of patients in the intervention group with improved recall memory at 6 months by 1 SD is at least 0.35. The effect size will be presented alongside a 95 % CI and *p* value. The proportion of patients in the control group displaying improved functioning by 1 SD will be used to highlight the learning effect.

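### As written, the primary one-sample test is tied to 0.35, the design alternative, and not to the 0.15 null on which the trial was sized

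*Protocol article*

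**What the plan says.** Under Sample size determination, the protocol article uses Fleming's single-stage procedure on the everolimus arm alone. The null is that "the proportion of patients in the intervention group who improve their memory function by 1 SD is at most 0.15"; the alternative is that "the proportion of patients in the intervention group who improve their memory function by 1 SD is at least 0.35". The error rates are "80 % power and a one-sided α of 0.05". The result is given as "we require a total sample size of 48 (i.e., 32 who receive the intervention and 16 control subjects", followed by "This sample size is inflated to allow for 20 % loss to follow-up".

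The same section sets out a guide with three zones for the proportion in the intervention group. Below 0.15, everolimus does not merit further study. At the top, "A proportion of at least 0.35 would provide sufficient evidence for further investigation of this intervention". Values in between go to the trial team for discussion.

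Under Statistical methods, Main analysis, the only sentence that defines the primary test says that a one-sample chi-square test will examine "whether the proportion of patients in the intervention group with improved recall memory at 6 months by 1 SD is at least 0.35". A 95% CI and a p value are to accompany the effect size. The figure 0.15 does not appear in that section.

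**The concern.** A one-sample test is defined by the value it tests against. The sample size section names 0.15 for that role. The analysis section attaches the test and its p value to 0.35 and nothing else. Taken literally, the design alternative has become the tested value.

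A test against 0.35 asks whether everolimus does better than the rate the trial was designed to detect. If everolimus performs exactly as planned, that test has no power beyond its own type I error, and a result that meets the design target would be reported as non-significant. The p value is the only one specified for the primary outcome, and the trial exists to inform whether larger trials should follow.

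**Working it through.** **Inputs** (all from Sample size determination): p0 = 0.15, p1 = 0.35, one-sided alpha 0.05, power 0.80, loss 20%, 2:1 allocation.

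**1. Reproduce the sample size.** Normal approximation for a single-stage one-sample design:

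n = [(z₀.₉₅·√(p0(1−p0)) + z₀.₈₀·√(p1(1−p1))) / (p1−p0)]²

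- 1.645 × √(0.15×0.85) = 0.587
- 0.842 × √(0.35×0.65) = 0.401
- (0.587 + 0.401)/0.20 = 4.944, squared = 24.44, rounded up to 25
- 25/0.80 = 31.25, rounded up to 32; plus 16 controls = 48

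This matches the stated figure, so the sample size is not in error. It depends on 0.15 being the null.

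**2. Numbers analysed.** Three cases are used: 25 (the uninflated size), 26 (80% of 32 is 25.6) and 32 (no loss).

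**3. Test against 0.35, true rate 0.35.** The statistic is z = (x − 0.35n)/√(n×0.35×0.65), and the probabilities are exact binomial upper tails. The article does not give the sidedness in the analysis section, so both versions are shown. For these n, the exact one-sided test has the same upper cut-off as the two-sided chi-square.

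| n | One-sided z: needs | Probability | Two-sided chi-square (upper side) or exact one-sided: needs | Probability |
|---|---|---|---|---|
| 25 | 13 (52%) | 6.0% | 14 (56%) | 2.5% |
| 26 | 14 (54%) | 3.8% | 14 (54%) | 3.8% |
| 32 | 16 (50%) | 5.8% | 17 (53%) | 2.7% |

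Favourable significance therefore occurs about 2.5 to 6% of the time.

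**4. Test against 0.15, true rate 0.35.** Now z = (x − 0.15n)/√(n×0.15×0.85).

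| n | Version | Rejects at | Type I error at 0.15 | Power at 0.35 |
|---|---|---|---|---|
| 25 | one-sided chi-square/z | 7 | 7.0% | 83% |
| 32 | one-sided chi-square/z | 9 | 4.1% | 84% |
| 25 | exact binomial | 8 | 2.5% | 69% |
| 26 | exact binomial | 8 | 3.2% | 74% |
| 28 | exact binomial | 8 | 4.9% | 82% |

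The chi-square version delivers the stated 80%, at the price of a true type I error above 5% with 25 patients. The exact version holds the 5% but reaches 80% power only at 28 evaluable, which after 20% loss is 28/0.80 = 35 randomised to everolimus.

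**5. The observed bar of 0.35.** When the true rate is 0.35, the chance of observing at least 0.35 is 53% with 25 patients (9 or more) and 43% with 26 (10 or more). The 80% power does not describe this event.

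**The case against.** The strongest reply is that the analysis sentence states no null at all. Its wording closely follows the alternative in the sample size section, where the null of 0.15 and the one-sided alpha are explicit, so it may simply be a loose restatement with 0.15 still intended. That is plausible, and it is why the point is limited to the text as written. It does not remove the conflict: the only number attached to the test is 0.35, and an analyst working from that section would use it.

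It can also be said that this is a proof-of-principle study whose objective is to estimate effect sizes, and that a 95% CI will be reported. That softens the consequence. At 9/25, for example, the Wilson interval is 0.20 to 0.55, so the excess over 0.15 would be visible whatever the p value. But the article disclaims power only for comparing drug with placebo; for the one-sample test it claims 80%.

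Two stronger readings are not supported:

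- A reader might infer that non-significance against 0.35 would count as success, so that an inert drug would often pass. Nothing in the article says so. A low observed proportion above 0.15 falls in the discussion zone, and with a true rate of 0.15 an observed 0.35 or more is reached only 0.8% (25 patients) or 0.3% (26 patients) of the time.
- A reader might set the 43 to 53% in step 5 against the stated 80% and call the decision guide underpowered. The 80% belongs to the hypothesis test. Missing the 0.35 bar leads to discussion, not to stopping: with a true rate of 0.35, the observed proportion falls below 0.15 only about 1% of the time. The zones need not coincide with the test's critical count.

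**Conclusion.** The point holds as a contradiction between the two sections. The sample size is right for a null of 0.15, and the analysis sentence ties the primary test to 0.35. Followed literally, a true rate equal to the design alternative would be significant in favour of everolimus about 2.5 to 6% of the time, against 83 to 84% for the one-sided chi-square against 0.15 with 25 or 32 patients.

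These figures assume 25, 26 or 32 everolimus patients analysed and no continuity correction for the chi-square; the 2.5 to 6% range covers both one-sided and two-sided versions. The conclusion does not depend on which of these applies. The article does not show that 0.35 was intended as the null, and the three-zone guide is not itself wrong. The wording should be corrected before unblinding because it governs the sole primary p value.

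**What to change.** In Main analysis, replace the test sentence with one that says: the one-sample test is of the null that the everolimus proportion is at most 0.15, at one-sided alpha 0.05; the proportion is reported with its 95% CI; and 0.35 is the design alternative.

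State the version of the test and its actual properties. Either choice is defensible if disclosed:

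- One-sided chi-square/z: with 25 evaluable it rejects at 7 or more, with 83% power and a true type I error of 7.0%.
- Exact binomial: with 25 evaluable it rejects at 8 or more, with a type I error of 2.5% and 69% power (74% at 26, 82% at 28). The stated 80% must then be restated for the number expected, or recruitment raised.

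In Sample size determination, the three zones can stay as a separate guide, including the discussion zone. Add a note that the 80% power refers to the test against 0.15 and not to observing 0.35 or more.

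The cost is protocol and analysis plan wording before unblinding. No new data are needed. Extra patients arise only if the exact test is chosen and 80% power is to be kept.

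### The primary test is designed as one-sided at 5%, but the analysis section names a chi-square test with no stated direction or level and a 95% CI that does not match it

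*Protocol article*

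**What the plan says.** Under Sample size determination, the article states "The sample size has been calculated on the basis of Fleming’s single-stage procedure [16". The null is that no more than 0.15 of everolimus patients gain 1 SD in memory function; the alternative puts that share at 0.35 or above. The error rates and total are given as "with 80 % power and a one-sided α of 0.05, we require a total sample size of 48", split as "32 who receive the intervention and 16 control subjects". On dropout the article says "This sample size is inflated to allow for 20 % loss to follow-up".

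The same section sets bands on the observed proportion in the intervention group. Below 0.15, further investigation is not warranted. At 0.35 or more, there is sufficient evidence for it. Anything between goes to the trial team for discussion.

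Under Main analysis, the article says "A one-sample chi-square test will be used to determine whether the proportion of patients in the intervention group". The sentence goes on to name 0.35 as the value to be reached, for a 1-SD gain in recall memory after 6 months. On reporting it adds: "The effect size will be presented alongside a 95 % CI and *p* value". That section states no direction and no significance level for the test, and it attaches no decision rule to the interval.

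**The concern.** The design fixes a direction (improvement) and an error rate (5% in that direction). The named analysis carries over neither. A one-degree-of-freedom chi-square statistic squares the deviation from the null, so its ordinary p value counts departures on both sides. A 95% CI pairs with a two-sided 5% test, which is one-sided 2.5%. The interval that pairs with a one-sided 5% test is a 90% CI or a one-sided 95% lower bound.

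Two analysts following the text in good faith could therefore report different p values for the same data, one below 0.05 and the other above it. The trial team, asked to weigh an intermediate result, would not know which of the two the design intended.

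**Working it through.** **Inputs.** Null p0 = 0.15, alternative p1 = 0.35, one-sided alpha 0.05, power 80%, loss 20%, intervention arm 32: all from Sample size determination. Test and interval: from Main analysis. The null used below is 0.15, the value on which the sample size rests.

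**Step 1: reproduce the sample size.** One-sample normal approximation:

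n = [(z_alpha × √(p0(1−p0)) + z_power × √(p1(1−p1))) / (p1−p0)]²

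with √(0.15 × 0.85) = 0.357, √(0.35 × 0.65) = 0.477 and z_power = 0.8416.

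- One-sided 5% (z = 1.645): n = 24.4, so 25 evaluable. 25 / 0.8 = 31.25, so 32. Adding 16 controls gives 48, the stated total.
- Two-sided 5% (z = 1.96): n = 30.3, so 31 evaluable. 31 / 0.8 = 38.75, so 39.

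Only the one-sided calculation gives 32, so the design is one-sided in substance as well as in words.

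**Step 2: apply the named test at 25 evaluable, 7 responders (28%).**

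- z = (0.28 − 0.15) / √(0.1275 / 25) = 1.82; chi-square = 3.31.
- Read one-sided: p = 0.034, reject 0.15.
- Ordinary chi-square p: 0.069, do not reject.
- 95% Wilson CI: 0.143 to 0.476, includes 0.15.
- 90% Wilson CI: 0.160 to 0.443, excludes 0.15.

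**Step 3: where else the readings differ.** The lowest count r with (r/n − 0.15) / √(0.1275/n) above 1.645 (one-sided) or 1.96 (two-sided) is:

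| n | One-sided cut-off | Two-sided cut-off | Discordant result |
|---|---|---|---|
| 24 | 7 | 8 | 7/24 = 29% |
| 25 | 7 | 8 | 7/25 = 28% |
| 26 | 7 | 8 | 7/26 = 27% |
| 29 | 8 | 9 | 8/29 = 28% |
| 30 | 8 | 9 | 8/30 = 27% |
| 31 | 8 | 9 | 8/31 = 26% |
| 32 | 9 | 9 | none |

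The cut-offs also coincide at 22, 23, 27 and 28. At 32, 8 responders give 0.057 one-sided and 0.113 two-sided (neither rejects); 9 give 0.019 and 0.038 (both reject).

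**Step 4: true error rates at 25, from the binomial distribution.**

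| Cut-off | P(reject) at 0.15 | P(reject) at 0.35 |
|---|---|---|
| 7 | 0.0695 | 82.7% |
| 8 | 0.0255 | 69.4% |

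The one-sided chi-square rule (cut-off 7) exceeds the stated alpha of 0.05. An exact one-sided 5% test has cut-off 8 at n = 25. At n = 32 its cut-off is 9, with type I error 0.041 and power 84.2%.

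**Step 5: test against interval when both are exact.** At 8/25 the exact one-sided p is 0.0255, yet the 95% Clopper–Pearson lower limit is 0.1495, just below 0.15. The 90% lower limit, 0.170, agrees with the test. At 9/32 the exact one-sided p is 0.041; the 95% lower limit is 0.1375 and the 90% lower limit 0.155. The interval mismatch therefore survives a change to an exact test.

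**The case against.** Main analysis never says the test is two-sided. The only level stated anywhere is the one-sided 0.05, nothing withdraws it, and a one-sided p value can be taken from the signed root of the chi-square. A reader might infer that the plan prescribes a two-sided 5% test in conflict with its design. The text does not support that: it is silent, and the two-sided reading comes from how a chi-square p value is ordinarily produced. This part of the objection stands, and the point is one of mismatch and ambiguity.

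A 95% CI shown for estimation beside a one-sided 5% test is ordinary practice, particularly in a trial whose stated aim is to estimate effect sizes. This also stands. The interval is a fault only if it is taken to decide the test.

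A reader might further infer that one responder flips the verdict on everolimus. It does not. The article's bands are set on the proportion, and every discordant result found here (26% to 32%, counting the exact case 8/25) lies between 0.15 and 0.35, where the team discusses the result.

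Nor should the power figures of 83% and 69% be read as the cost of two-sidedness. The higher figure belongs to a cut-off that breaks the stated alpha. A valid exact one-sided test at 25 already has cut-off 8 and power of about 69%.

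Finally, the analysis set can reach 32 on everolimus, where the large-sample readings agree. And the value named in Main analysis is 0.35, against which 7/25 gives a chi-square p of 0.46. That reference value is a separate and larger inconsistency. Correcting it to 0.15 would still leave sidedness and interval level unstated.

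**Conclusion.** The point holds in a limited form. The design test is one-sided at 0.05 against 0.15. The named analysis is a non-directional chi-square with no stated sidedness or level, reported with an interval that matches a stricter one-sided level. At the planned 25 evaluable patients neither reading of the chi-square serves the design well: read one-sided, its true type I error is 7.0%; read in the ordinary way, it is not the one-sided 5% test that was sized. The two differ by one responder at 24 to 26 and 29 to 31 patients.

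These figures assume a null of 0.15, no continuity correction and, for the main example, exactly 25 evaluable. The consequence is confined to the evidence that the trial team would weigh in its discussion band. Severity is minor to moderate.

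**What to change.** In Main analysis, or in the SAP, replace the chi-square sentence with a one-sided exact binomial test at alpha 0.05, in the direction of improvement, of the null that the proportion is at most 0.15. This requires reconciling the 0.35 now named there with the design null. Give a 90% Clopper–Pearson CI, or a one-sided 95% lower bound, as the interval that matches the test. Keep the 95% CI as a descriptive estimate and label it so.

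State the operating characteristics that follow: at 25 evaluable, cut-off 8, type I error 0.0255 and power about 69% at 0.35; at 32, cut-off 9, type I error 0.041 and power about 84%.

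The change takes a few sentences and needs no extra patients or data. Its one cost is candour about power: at 25 evaluable the stated figure falls below the planned 80%.

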#### Secondary analyses

Secondary outcomes will be presented descriptively at baseline and 6 months, and effect sizes will be determined. The effect (between baseline and 6 months) of the control and intervention arms on wider aspects of neurocognitive function, seizures and daily life will be similarly assessed. Secondary analyses will consider both the primary and secondary outcome measures as dimensions of memory function as continuous variables rather than just the proportion of improved patients over time. In further modelling, we will use repeated-measures multivariate analysis of variance to model patterns of functioning over time at baseline and at 3 and 6 months. In these analyses, we will compare the scores from each neurocognitive test at 6 months between the intervention and control arms and will adjust for the balancing factors. The result will be presented as the (adjusted) difference in test outcomes between the intervention and control groups, along with 95 % CI and *p* value. The use of composite measures of these scales will be explored.

## Discussion

This proof-of-principle trial will be the first to determine the effect sizes of treatment with everolimus or placebo for 6 months for recall memory and executive function in adults with tuberous sclerosis. The goal is to provide evidence for whether larger trials for this indication in an adult population are appropriate.

The findings of this study will advance current knowledge in terms of understanding and treatment of tuberous sclerosis. Participants who receive this intervention have the potential for an amelioration of the neurocognitive deficits associated with tuberous sclerosis. Additional potential benefits exist, as mTOR inhibitors have been shown to reduce the size of renal AMLs that are present in most adults with tuberous sclerosis [11, 13] and also to improve the characteristic facial rash (facial angiofibromatosis) [30]. Wider potential benefits to society include reduced demand on carers and on health and social care services, as well as insights into the mechanistic basis for these problems in patients with tuberous sclerosis and potentially other patient groups.

## Trial status

The trial is sponsored by Cardiff University and is currently ongoing and open to recruitment. The manuscript of this report was drafted according to version 9.0 (15 January 2015) of the trial protocol. The protocol was written according to the SPIRIT statement. The final report will be written in accordance with the Consolidated Standards of Reporting Trials (CONSORT) statement.

## Abbreviations

AE, adverse events; AED, anti-epileptic drug; ALT, alanine aminotransferase; AML, angiomyolipoma; AST, aspartate aminotransferase; BIRT, Brain Injury Rehabilitation Trust; CANTAB, Cambridge Neurocognitive Test Automated Battery; CONSORT, Consolidated Standards of Reporting Trials; CRN, Clinical Research Network; CTCAE, Common Terminology Criteria for Adverse Events; CYP3AE, cytochrome P450 3AE; DMC, Data Monitoring Committee; DTI MR, diffusion tensor imaging magnetic resonance imaging; FEV_1_, forced expiratory volume in 1 second; GFR, glomerular filtration rate; IDED, intra-dimensional/extra-dimensional; IMP, investigational medicinal product; INR, international normalised ratio; LMW, low molecular weight; mTOR, mammalian target of rapamycin; mTORC1, mammalian target of rapamycin complex 1; PIS, patient information sheet; RSI, reference safety information; SAE, serious adverse event; SmPC, summary of product characteristics; SPIRIT, Standard Protocol Items: Recommendations for Interventional Trials; SRS-A, Social Responsiveness Scale – Adult version; TAND, tuberous sclerosis-associated neuropsychiatric disorders; TSA, Tuberous Sclerosis Association; TSC, tuberous sclerosis complex; ULN, upper limit of normal; WASI, Wechsler Abbreviated Scale of Intelligence
